#### **(4) OARSI Responder Criteria**

[ Time Frame: At weeks 4 after randomization.]

Responder criteria included: 1) greater than or equal to 50% improvement in WOMAC pain or WOMAC function and an absolute improvement of greater than or equal to 20, or 2) improvement in at least 2 of the following 3 scores: 20% improvement in pain and absolute change  $\geq 10$  on WOMAC pain score, 20% improvement in pain and absolute change  $\geq 10$  on WOMAC function score, or moderate or greater improvement ( $\leq 4$ ) on a 15 point global rating of change scale.

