#### **(3) Change in Patient Global Assessment (PGA)**

[ Time Frame: Change from baseline at 4 weeks, ***8 weeks*** and 16 weeks]

The PGA rating is a 11-point Numeric Rating Scale (NRS) in which participants will rate the degree to which their knee condition has changed from the time treatment was initiated to the present. The participant responds to the following query: “Please rate your overall knee’s condition from the time you began treatment until now.” using an 11-point NRS with 0 representing “A very great deal better” and 10 representing “A very great deal worse”.

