### **Additional file 3- The response rate defined by the Outcome Measures in Rheumatology Clinical Trials and Osteoarthritis Research Society International (OMERACT-OARSI)**

The response rate was defined as the proportion of patients who achieved the following criteria at week 4: 1)  $\geq 50\%$  improvement in WOMAC-pain or WOMAC-function and an absolute improvement of  $\geq 20$ , or 2) improvement in at least 2 of the following 3: 20% improvement in pain and absolute change  $\geq 10$  on WOMAC-pain, 20% improvement in pain; absolute change  $\geq 10$  on WOMAC-function; or moderate or greater improvement ( $\leq 4$ ).

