### **7. Outcome Definitions**

**Primary Outcome** The change in the total Western Ontario and McMaster University Osteoarthritis Index (WOMAC) from baseline to 4 weeks

**Secondary Outcomes** The secondary outcomes covered pain, physical function, and patients' overall assessment of disease severity.

- **Pain Dimensions** WOMAC pain (the change between the baseline and 4, 8, and 16 weeks), the worst knee pain in the last 24 hour using NRS(the change between the baseline and 4, 8, and 16 weeks) ;

- **Function Dimensions** the average function of previous week using WOMAC function (the change between the baseline and 4, 8, and 16 weeks), WOMAC stiffness (the change between the baseline and 4, 8, and 16 weeks), 30 Second Time Chair Rise Test (the change between the baseline and week 4), Timed Up and Go Test Time (the change between the baseline and week 4), One Leg Standing Test (the change between the baseline and week 4);
- **Patients' overall assessment of disease severity:** the 12-item Short Form Health Survey (the change between the baseline and 4, 8, and 16 weeks), the patient global assessment (the change between 4, 8, and 16 weeks);
- **Criteria of Response Rate:** The OMERACT-OARSI responder criteria to assess the response rate of treatment for KOA at 4 weeks.
- **The blinding assessment**

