**Additional file 6 - WOMAC-total and Sub-Domain Scores, Differences Between Groups, at week 4 (Per Protocol set)**

| Outcomes                           | Tuina
(n=63) | mPT
(n=64) | Between-group comparison
Mean difference (95% CI) | P value |
|-------------------------------------------|-------------------------|-----------------------|--------------------------------------------------------------|----------------|
| Primary outcome                    |                         |                       |                                                              |                |
| WOMAC-Total, mean (SD)             |                         |                       |                                                              |                |
| Baseline                                  | 19.10 (13.52)           | 19.42 (13.62)         | -0.33 (-5.09, 4.44)                                          | 0.892          |
| Week 4                                    | 13.44 (12.46)           | 13.58 (12.70)         | -0.13 (-4.55, 4.29)                                          | 0.952          |
| Mean change from baseline-week 4 (95% CI) | -5.65 (-8.33, -2.97)    | -5.84 (-9.56, -2.12)  | 0.19 (-4.36, 4.74)                                           | 0.933          |
| WOMAC-Pain, mean (SD)              |                         |                       |                                                              |                |
| Baseline                                  | 4.49 (2.80)             | 4.64 (2.98)           | -0.15 (-1.17, 0.87)                                          | 0.773          |
| Week 4                                    | 2.75 (2.38)             | 3.06 (2.62)           | -0.32 (-1.20, 0.56)                                          | 0.478          |
| Mean change from baseline-week 4 (95% CI) | -1.75 (-2.44, -1.05)    | -1.58 (-2.37, -0.78)  | -0.17 (-1.21, 0.88)                                          | 0.751          |
| WOMAC-Stiffness, mean (SD)         |                         |                       |                                                              |                |
| Baseline                                  | 1.71 (1.88)             | 1.42 (1.60)           | 0.29 (-0.32, 0.91)                                           | 0.347          |

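### The OMERACT-OARSI responder rule does not work as written on the WOMAC scores the trial reports: pain response is almost ruled out, the function item tests pain, and the global item uses a scale described nowhere else

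*Supplement*

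**What the plan says.** The rule appears twice in current text: in the amended protocol (Secondary Outcome Measure 4, OARSI Responder Criteria) and in Additional file 3.

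- **Route 1** (amended protocol): "greater than or equal to 50% improvement in WOMAC pain or WOMAC function and an absolute improvement of greater than or equal to 20". Additional file 3 uses the same cut-offs.
- **Route 2, pain and function items.** Two of three items are needed. In the amended protocol the text runs "on WOMAC pain score, 20% improvement in pain and absolute change" and then gives the 10-point cut-off for function. The percentage attached to the function item is therefore a percentage of pain. Additional file 3 punctuates this differently: "20% improvement in pain; absolute change" of at least 10 on function. There the function item has no percentage criterion of its own.
- **Route 2, global item.** The amended protocol requires a value of 4 or less "on a 15 point global rating of change scale". Additional file 3 keeps the cut-off ("or moderate or greater improvement", 4 or less) but names no scale.
- **Global instrument described.** Secondary Outcome Measure 3 says "The PGA rating is a 11-point Numeric Rating Scale (NRS"), running from 0 (best) to 10 (worst). No 15-point scale is described anywhere else.
- **SAP.** Section 7 lists "The OMERACT-OARSI responder criteria to assess the response rate of treatment for KOA at 4 weeks", and section 8 compares the arms by chi-squared or Fisher's exact test. Neither section gives a derivation, a WOMAC range or a rescaling step.

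**The concern.** An absolute cut-off has meaning only on a stated scale. If the 10- and 20-point cut-offs are applied to WOMAC scores in the units the trial tabulates, most patients cannot meet the pain parts even if they become pain-free. The endpoint would then depend mainly on who started with a high function score. The other two faults add to this. A function item that tests pain does not measure functional response, and a global item on an undescribed scale leaves the programmer to choose. Two programmers following the two current texts could report different response rates from the same data. At stake are the week-4 response rate and its between-group test.

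**Working it through.** **No plan figure to reproduce.** The plan states no expected response rate. Its one design figure, 140 patients, rests on WOMAC total: a two-sample t calculation with difference 7, SD 13, two-sided 5% and 80% power gives 56 per arm, and 56/0.8 = 70. The responder rule plays no part in it.

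**Step 1: which scale are the scores on?** Baseline means, pain + stiffness + function against total:

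| Group (source) | Sum | Total |
|---|---|---|
| Provided primary outcome, n = 127 (Additional file 5) | 4.57 + 1.57 + 13.13 = 19.27 | 19.26 |
| Tuina, n = 63 (Additional file 6) | 4.49 + 1.71 + 12.89 = 19.09 | 19.10 |
| mPT, n = 64 (Additional file 6) | 4.64 + 1.42 + 13.36 = 19.42 | 19.42 |

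The subscales add to the total within rounding, so they look like plain sums and not subscales each put on a common range. This is an inference, because the documents never state the range.

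**Step 2: who could meet each cut-off?** If the minimum score is 0, improvement cannot exceed baseline. Inputs are from Additional file 5: pain 4.57 (SD 2.88) and function 13.13 (SD 10.06). For cut-off c, k = (c − mean)/SD. The normal share is P(Z ≥ k). The gamma share uses the same mean and SD. The bound for any distribution (Cantelli, for k > 0) is 1/(1 + k²).

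| Baseline | k | Normal | Gamma | At most |
|---|---|---|---|---|
| Pain ≥ 10 | (10 − 4.57)/2.88 = 1.89 | 3.0% | 5.2% | 22% |
| Pain ≥ 20 | (20 − 4.57)/2.88 = 5.36 | about 0% | 0.05% | 3.4% |
| Function ≥ 10 | (10 − 13.13)/10.06 = −0.31 | 62% | 53% | not applicable |
| Function ≥ 20 | (20 − 13.13)/10.06 = 0.68 | 25% | 20% | 68% |

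These patients did have pain to lose. Entry required at least 4 on the 0-10 pain scale (Additional file 2), and the mean baseline NRS was 5.90.

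**Step 3: observed change at week 4** (Additional file 6). SD of change = CI half-width / t(0.975, n − 1) × √n.

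- Pain, Tuina: mean fall 1.75, SD 0.695/1.999 × √63 = 2.76. P(fall ≥ 10) = P(Z ≥ 2.99) = 0.14%.
- Pain, mPT: mean fall 1.58, SD 0.795/1.998 × √64 = 3.18. P(fall ≥ 10) = P(Z ≥ 2.65) = 0.41%.
- Expected count for pain: 63 × 0.0014 + 64 × 0.0041 = 0.35, so fewer than one patient in 127.
- Function, by the same method (SD 7.74 and 11.11): fall ≥ 10 in 20% and 29%; fall ≥ 20 in 1.7% and 7.5% (about 1 and 5 patients).

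**Step 4: how much does the unstated range matter?** The maxima here are assumed, since the documents give none. If raw pain runs to 20, ten points on a 0-100 scale equal 2 raw points, and 45-46% of patients reach it. If raw pain runs to 50, they equal 5 raw points, and 12-14% reach it. With the cut-off applied to the raw sums, 0.1-0.4% reach it.

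**Step 5: can the global cut-off be carried over to the PGA?** Not from the documents. Proportional mapping depends on the coding assumed for the 15-point scale and on 5 meaning no change on the PGA. Coding 1-15 with 8 as no change gives 5 − 5 × (8 − 4)/7 = 2.1. Coding 0-14 with 7 as no change gives 5 − 5 × (7 − 4)/7 = 2.9.

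**The case against.** Several stronger readings are tempting, and the documents do not support them.

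- **That the 15-point scale was never collected.** Table 4 of the amended protocol has its own week-4 row for the responder criteria, separate from the PGA row, and the case report form is not shown. The scale may have been recorded there. What stands is that it is described nowhere else.
- **That the global item is too lenient.** This would follow only if the cut-off of 4 were read on the 0-10 PGA. No text does so, and the global item alone cannot make a responder.
- **That patients were in fact misclassified.** No responder counts or derivation are shown. Additive tables show how scores were reported, not the units used for the responder derivation. If the scores were rescaled first, that step is undocumented.
- **That the whole rule is unreachable.** The mismatch is near-total for pain but only partial for function, since 53-62% start with function of at least 10.
- **That the comparison is biased.** The same rule applies to both arms, and their baseline function is close (12.89 and 13.36). Lost sensitivity is plausible; a shift towards one arm is not shown.

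It may also be said that the 0-100 scale is not in the documents. That is so, and it should be confirmed against the criteria the protocol cites. These points limit the finding but do not rescue the rule: neither current text has a percentage criterion for function, and neither says on what scale 10 and 20 points apply.

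**Conclusion.** The rule is wrong as written, with moderate severity. Applied to the reported WOMAC scores, it almost rules out response on pain: about 3-5% of patients could improve by 10 points (at most 22% under any distribution) and essentially none by 20. Route 1 then works almost only through function, open to about 20-25%. With the pain item so rarely reachable, route 2 mostly needs both the function item, which in the protocol tests pain, and a global item whose scale is not described.

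This rests on four assumptions: the scores are raw sums with minimum 0; the 20-point requirement in route 1 applies to the same subscale as the 50% requirement; baseline shapes are near normal or gamma; and the patients with week-4 data represent the trial. The function percentages are the least certain, because the SD is close to the mean. One secondary outcome is affected. The primary outcome and the sample size are not.

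**What to change.** 1. State the WOMAC version and the range of each subscale. Apply the 20- and 10-point cut-offs to pain and function normalised to a common scale, for example 0-100, after confirming the intended scale against the cited criteria.
2. Reword the second item of route 2 so that it requires at least 20% improvement in function together with an absolute change of at least 10 in WOMAC function.
3. Name the global instrument actually collected and pre-specify a cut-off justified for that instrument. If it is the PGA, the documents do not yield a value; the mapping above gives roughly 2 to 3, depending on the assumed coding.
4. Put one identical definition in the amended protocol, Additional file 3 and the SAP.

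The cost is wording and a derivation line in the analysis program. The WOMAC corrections use scores already collected; the global item needs only a statement of which instrument was recorded.

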#### **(5) Change in 30 second time chair rise test**

***[ Time Frame: Change from baseline at 4 weeks]***

***Participants will be seated with their arms crossed in front of their chest. On the command "go" participants will stand up and sit down for as many trials as they can in a 30 second period.***

#### **(6) Change in Timed Up and Go Test Time**

***[ Time Frame: Change from baseline at 4 weeks]***

***On the command “go” participants will stand up from a chair, walk 3 meters, turn around, return to the chair and sit down. The time it takes to complete this task will be recorded.***

#### **(7) Change in One Leg Standing Test**

***[ Time Frame: Change from baseline at 4 weeks]***

*One single-leg standing was assessed balance. Test required the subject to stand with arms by his/her side. Timing was started when the subject raised one foot off the ground. Timing was stopped if the subject displaced the weight-bearing foot, touched the suspended foot to the ground, used the suspended limb to support the weight-bearing limb, or reached the maximum balance time of 30 seconds.*

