#### 4. The Target Number of Participants and Estimation Basis

- (1) Estimation of the number of patients: The following is assumed using the reference literature of prior studies to estimate the number of patients.
- (2) Level of significance,  $\alpha_{\text{two-sides}} = 0.05$ .
- (3) Type 2 error ( $\beta$ ) is set to 0.2, and the power of the test is set to 80%.
- (4) Based on our pilot study and the previous studies about the minimal clinically important difference (MCID) [28, 29], we assumed that the primary outcome (a total WOMAC score at 4 weeks) in Tuina group was expected to have mean difference of 7 to mPT with a standard deviation for both groups of 13.
- (5) Compliance: 80% (the ratio expected to receive treatment 8 times or more during the 3-week treatment period).
- (6) Sample size calculation for the trial by using PASS 15 (Power Analysis and Sample Size Software (2017). NCSS, LLC. Kaysville, Utah, USA, [ncss.com/software/pass](http://ncss.com/software/pass).)

As a result of applying (1), (2), (3), (4), and effect size, the sample size is calculated to be 140 in total, 70 patients in each group.

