### **4. Level of statistical significance and Confidence intervals to be reported**

All applicable statistical tests will be 2-sided and will be performed using a 5% significance level. All confidence intervals will be 95% confidence intervals.

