## 8. Analysis methods

We will use intention-to-treat analyses, analyses will be conducted by a statistician blinded to treatment allocation, with two-sided hypothesis tests. Changes from baseline will be presented for each group at each time point using the mean change and 95% confidence intervals.

**Primary outcome** Primary outcome will apply the repeated measures analysis of variance. Age, sex, BMI, baseline WOMAC score, medication as the covariates. The mean difference in change from baseline to 4 weeks of WOMAC total as the dependent variables, and group (Tuina group and mPT), time (baseline, week 4, 8 and 16), and the group  $\times$  time interaction as independent variables. The approximate normality and Mauchly's test of sphericity were examined. Then the interaction of group-interaction term was tested first. If significant, between-group differences at each time point were tested. If not significant, the treatment main effect was tested next.

**Secondary outcomes** For repeated measures of continuous outcome, including the subscale of WOMAC, NRS, SF-12 and PGA, will be estimated using the repeated measures analysis of variance, 30 Second Time Chair Rise Test, TUG and One Leg Standing Test will be applied with an independent t test for normal distribution, Mann-Whitney U test for unnormal distribution. And for categorical variables- responder criteria, will be compared across groups with the  $\chi^2$  tests or Fisher's exact test.

**Blinding outcome** Blinding assessment will apply the James blinding index with the blinding package of SAS software.

**Effect size** Effect size will be computed with mean group-difference/baseline SD; **MCID** The minimal clinically important difference (MCID) of WOMAC- total is set as 14%, which will be calculated with the change of baseline and the corresponding evaluation time point/baseline

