|---------------------------------------------------------|--------------------|-------------------|-------|
| SF-12, mean (SD)                                 |                    |                   |       |
| Physical health                                         | 37.41 (8.34)       | 37.85 (7.55)      | 0.746 |
| Mental health                                           | 48.23 (10.02)      | 51.39 (9.41)      | 0.057 |
| 30 Second Time Chair Rise Test, mean (SD), times | 10.08 (3.98)       | 10.96 (3.62)      | 0.667 |
| Timed Up and Go Test Time, mean (SD), second     | 11.24 (1.84)       | 11.30 (2.96)      | 0.906 |
| One Leg Standing Test, mean (SD), second         | 21.95 (11.36)      | 18.76 (10.63)     | 0.928 |
| Target knees, No. (%)                            |                    |                   |       |
| Left                                                    | 6 (46.15%)         | 60 (47.24%)       | 0.940 |
| Right                                                   | 7 (53.85%)         | 67 (52.76%)       |       |
| Credibility/Expectancy Questionnaire, mean (SD)  |                    |                   |       |
| Credibility questionnaire                               | -0.17 (-0.70,0.47) | 0.28 (-0.40,0.74) | 0.20  |
| Expectancy questionnaire                                | 0.59 (-0.79,0.72)  | 0.13 (-0.78,0.58) | 0.96  |

**Note:** a: Seven patients in the Tuina group, 6 in the mPT group, did not complete the primary outcome – WOMAC-total at week 4. b: 63 patients in the Tuina group, 64 in the mPT group, complete the primary outcome – WOMAC-total at week 4. *p*-values based on t-tests for continuous characteristics and chi-squared tests for categorical characteristics.

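### The One Leg Standing Test is capped at 30 s, but the SAP tests its raw change score with no baseline covariate and no handling of capped values

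*Supplement*

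**What the plan says.** The test is defined in the Protocol with Amended Changes, Secondary Outcome (7). Timing ends on loss of balance "or reached the maximum balance time of 30 seconds", and the outcome is the change from baseline at 4 weeks. SAP section 7 repeats this: "One Leg Standing Test (the change between the baseline and week 4". SAP section 8 gives the analysis: "One Leg Standing Test will be applied with an independent t test for normal distribution, Mann-Whitney U test for unnormal distribution".

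The covariates in SAP section 8 (age, sex, BMI, baseline WOMAC, medication) are listed for the primary outcome only. Neither document gives a rule for values at 30 s, a baseline adjustment for this test, or a plan to report how many patients reach the cap.

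Additional file 5 gives the baseline mean (SD): 18.76 (10.63) s in the 127 patients with the week-4 primary outcome and 21.95 (11.36) s in the 13 without it.

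**The concern.** A value stopped at 30 s is right-censored. Subtracting baseline from week 4 treats it as exact. A patient at 30 s at entry cannot have a positive change, and a patient at 30 s at both visits scores exactly 0 whatever happened to balance. Moving to Mann-Whitney does not help, because ranks of the change still put these patients below every improver.

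This is the trial's only balance outcome. If many patients start at or near the cap, the difference in seconds is pulled towards zero. A null result could then be taken as evidence that the two therapies act equally on balance, when the scale had little room to show a difference.

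**Working it through.** **Plan's own figure.** None exists for this test. The sample size of 140 rests on WOMAC total ("mean difference of 7 to mPT with a standard deviation for both groups of 13"). The normal formula gives 2 × (1.96 + 0.842)² × 13² / 7² = 54.1, so 55 per arm. The t-based value is 56, and 56 / 0.80 = 70 per arm. That reproduces the stated size and is not affected by this point.

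**Pooled baseline.**
- Mean = (127 × 18.76 + 13 × 21.95) / 140 = 19.06 s.
- SD = √[(126 × 10.63² + 12 × 11.36² + between-group part) / 139] = √(15906 / 139) = 10.70 s.

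**Does the spread suggest a ceiling?** A flat distribution on 0-30 s has SD 30/√12 = 8.66. Both 10.63 and 10.70 exceed it, so values lie towards the extremes. With a mean well above 15, the upper end is the likelier one.

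**Share at the cap.** Assume a latent time X, recorded as X limited to 0-30, and solve for the parameters that return the reported mean and SD.
- Normal, all 140: μ = 21.50, σ = 16.51. Share = 1 − Φ((30 − 21.50) / 16.51) = 1 − Φ(0.515) = 30%.
- Normal, the 127: μ = 20.85, σ = 15.93. Share = 1 − Φ(0.574) = 28%.
- Weibull: 35% (127) and 37% (140). Log-normal: 37% and 39%.
- With no shape assumed, the mean, SD and range allow 0 to 47% (127) or 0 to 49% (140).
- A beta distribution with nobody exactly at 30 s still puts about 43% above 25 s and 31% above 28 s.

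**Loss of a gain in one arm.** Add a gain g to X, re-limit to 0-30, and divide the observed mean gain by g. For small g, the share kept is about the share strictly inside the range: under the normal fit, 1 − 0.303 − 0.096 = 0.60. The 0.096 is the floor at 0 s, which the Weibull and log-normal fits do not have. For uniform gains of 2-5 s, all fits keep 57-64%, so 36-43% is lost.

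**Loss of a between-arm difference when both arms gain.** Assume 3 s in the comparator and a further d in the other arm (140 patients).

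| True d | Observed, normal | Observed, log-normal |
|---|---|---|
| 4 s | 2.12 s (53%) | 2.23 s (56%) |
| 5 s | 2.60 s (52%) | 2.76 s (55%) |
| 8 s | 3.94 s (49%) | 4.25 s (53%) |

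**Effect on the test.** The cap also shrinks the SD of change, to about 0.69-0.77 of its uncapped value, so the standardised effect keeps 68-82%. Take 63 per arm (Additional file 5: "63 patients in the Tuina group, 64 in the mPT group, complete the primary outcome"; similar numbers are assumed for this test), the normal fit, a true 4 s difference and an assumed baseline/week-4 correlation of 0.85. Power then falls from about 70% on uncapped change to 42-50% (t test) or 40-49% (Mann-Whitney).

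**Alternatives, simulated with 63 per arm.**

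| Setting | t on change | ANCOVA, capped seconds | Tobit with baseline |
|---|---|---|---|
| Log-normal, log effect 0.5, correlation 0.6 | 0.42 | 0.60 | 0.62 |
| Log-normal, log effect 0.5, correlation 0.8 | 0.62 | 0.76 | 0.80 |
| Normal, 5 s, common gain 3 s, correlation 0.6 | 0.32 | 0.43 | 0.48 |

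The log-normal rows use 600 replicates. The last row uses 300, so its standard error is about 3 points, and its Tobit model also treats 0 s as left-censored. In that row the mean estimate of the true 5 s was 2.7 (change), 2.7 (ANCOVA) and 5.2 (Tobit). Tobit type I error was 0.05-0.06. Baseline adjustment brings most of the power; only the censored model recovers the size of the effect.

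**The case against.** The strongest reply has four parts.

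- **The share at the cap is modelled, not reported.** This stands. A reader might infer that 30-40% of patients demonstrably start at 30 s, but the documents fix no figure. The source row is also imperfect. Its printed P value is 0.928, while a t test on its means and SDs gives t = 3.19 / (10.70 × √(1/127 + 1/13)) = 1.02, P = 0.31. So either the P value or the summaries are wrong.
- **A reader might infer that the cap halves any real gain.** The figures do not support this. A uniform gain in one arm loses 36-43%. Near-halving applies to the between-arm difference, and only if the comparator also gains. That is plausible, since both arms are treated and given home exercise, but it is an assumption. The standardised effect loses less, 18-32%. Nor does the SAP label these patients as not improved; it only gives them a numeric change of 0 or below.
- **Most of the power gain is ordinary baseline adjustment.** This also stands. Censoring itself adds only a few points (about 2-10 in simulation).
- **Seconds held within a 30 s test is a legitimate bounded outcome, and Tobit extrapolates beyond it.** This is fair as a choice of estimand, but the plan does not make that choice. It does not say that its difference in seconds is limited by the cap.

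The defect itself is not answered: nothing in the plan deals with capped values.

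**Conclusion.** The point holds in limited form. The cap, the change-score outcome, the unadjusted tests and the absence of any ceiling rule are all in the text, and a change of 0 or below for anyone starting at 30 s is arithmetic. The size is conditional: about 28-39% at the cap, 36-43% of a uniform one-arm gain lost, and up to about half of a between-arm difference lost if both arms gain. These figures rest on assumed latent shapes, gains and correlations, and on a baseline row with an inconsistent P value. The trial data would replace the first figure by a simple count.

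A reader might go further and see a threat to the trial's main conclusion. The documents do not support that: this is one secondary outcome, and neither the WOMAC analysis nor the sample size depends on it. It should be put right, with moderate confidence in the stated size.

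**What to change.** In SAP sections 7 and 8:

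1. Take the One Leg Standing Test out of the t/Mann-Whitney sentence.
2. Analyse week-4 time as right-censored at 30 s, for example by Tobit regression, with group, baseline time and an indicator for baseline at 30 s.
3. Keep ANCOVA on capped seconds as a sensitivity analysis.
4. Report the number and share at 30 s by arm at baseline and week 4.
5. Check the P value for this test in Additional file 5 against the means and SDs.

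Two substitutes should be avoided. An unadjusted rank test on the week-4 value discards baseline: at correlation 0.8 with the normal fit, power fell from about 0.47 (Mann-Whitney on change) to about 0.33. A Cox model of time to loss of balance is possible, but it is not equivalent to Tobit, because it estimates a hazard ratio and not a difference in time.

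The cost is SAP wording and one extra model on data already collected. The downside is that Tobit assumes a distribution above 30 s that cannot be checked, which is why the capped-seconds ANCOVA should stand beside it.
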